**3.9 Laboratory methods**

**Specimen collection**

GPs take combined throat and nose swabs which will be sent from sentinel GP surveillance networks to the usual laboratory.

**Tests used**

Influenza laboratory confirmation will be undertaken using comparable real-time PCR assays. Samples undergo a molecular analysis for circulating influenza A and influenza B viruses, respiratory syncytial viruses A and B, human metapneumoviruses A and B and COVID-19. Further analyses including that for seasonal coronaviruses, rhinovirus, adenovirus may be carried out. Further influenza genetic characterisation work is undertaken to determine genetic clade, and for influenza B viruses the lineage.

**3.10 Statistical Analysis**

Stata 14/17 (StataCorp, College Station, TX, USA) will be used for this data analysis.

**Flu and RSV descriptive analyses**

Cases and non-cases will be described according to:

- Month of swab – count (%)
- Sex – count (%)
- Age group – count (%)
- Region - count (%)
- Risk status – count (%)
- Vaccination Status including Vaccination Type – count (%)
- Past season vaccination status – count (%)
- COVID-19 vaccination status – count (%)

Differences in swab positivity within these groups will be tested using Chi-squared or Fisher’s exact test, as appropriate. Swabs with a gap from onset to swab >7d, and swabs taken less than 14days (21days for children) of vaccination will not be included in descriptive analyses.

**Flu TNCC**

For analysis of this test-negative case-control study, logistic regression will be used to calculate the unadjusted odds ratios for influenza vaccination in cases compared to controls, with a 95% confidence interval. This will be used to calculate an unadjusted VE as unadjusted VE=1-OR.

Logistic regression will be used to calculate the odds ratio for vaccination, adjusted for week of swab, scheme and age group, and additionally for relevant characteristics which change the vaccine effect by ≥1% (including risk status and sex). This will be used to calculate the adjusted VE. This will be undertaken for all cases/controls in the elderly, working-age adults and children separately, and in relevant subgroup analyses.

**Missing data**

We will aim to use multiple imputation methods for our main analysis where possible, rather than exclude data. However, data on vaccination status, age group and date of swab must be complete for inclusion in the study.

*Multiple imputation for missing risk status*

Multiple imputation methods will be used for missing data on risk status, taking into account patient age, and vaccination history and age eligibility.

*Multiple imputation for missing onset date*

Multiple imputation will be used where onset dates are missing. An interaction term between vaccination status and indicator for swab within 0-7days of onset will fitted (the sample size needs to remain consistent). Where onset is missing this indicator will be imputed based on the proportion of samples with known onset falling within the 7day window, taking into account positivity for flu or other viruses and patient age.

*Multiple imputation for missing vaccination date*

Where an adult patient has indicated that they were vaccinated at the time of the swab, but no vaccination date was given, a hot-deck imputation approach will be used. Vaccination dates will be sampled from other vaccinated patients within the same broad age cohort (18-64 or 65+) and swabbed within the same week. The imputed vaccination dates will be used to assign patients as within 1-13 days of vaccination or fully vaccinated.

In secondary analyses by vaccine type, a category for unknown vaccine type will be included. (Since vaccine type is almost universally missing for patients whose vaccination date is missing, the above imputation approach for vaccination dates need not be taken for analyses of vaccine type).

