**Study Site Settings**

| English RCGP/UKHSA scheme:  Patients who contacted their GP, where the GP was part of the Royal College of General Practioners Research and Surveillance Centre (RCGP-RSC) sentinel scheme, and who had a sentinel respiratory swab taken with a result for influenza during the 2023/24 influenza season. Indications for swabbing are influenza-like illness, COVID19-like illness, an acute respiratory infection or exacerbation of asthma/COPD with onset within the last 10 days. Patients are either swabbed and consented by their GP as part of a face-to-face consultation, or directed to take a postal self-swab by GPs through takeatestuk.com after being issued a voucher code. All sentinel swabs are tested for respiratory infections including influenza and RSV using RT-PCR at UKHSA’s Virus Reference Laboratory. Vaccination data are available via linkage to GP records. |
| --- |

| Scottish PHS scheme:  Patients who contacted their GP, where the GP was one of around 140 sentinel practices taking part in the CARI surveillance programme, and who had a respiratory swab taken with a result for influenza during the 2022/2023 influenza season. Indications for swabbing were acute respiratory infection (ARI) with sudden onset within the last 7 days, and aligning with the ECDC definition of ARI. Patients are either consented and swabbed by their GP face-to-face, or they use a self-swabbing kit to take the swab themselves. All sentinel swabs are multiplex tested for 10 respiratory infections at the West of Scotland Specialist Virology Centre and results are held by ECOSS (national database of all virology test results). Vaccination data are available for adults only from the Vaccine Management Tool (VMT). All date can be record-linked using the CHI number. |
| --- |

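### As worded, each of the three influenza imputation models leaves out a variable that the VE analysis needs, so the main VE estimates can be biased by an amount the documents do not let one fix

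*Protocol*

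**What the plan says.** All references are to Study 2 (influenza), section 3.10, unless stated.

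- **Role of imputation** (Missing data): "We will aim to use multiple imputation methods for our main analysis where possible, rather than exclude data".
- **Analysis model** (Flu TNCC): logistic regression of influenza status on vaccination, always adjusted for week, scheme and age group. Further covariates are kept by a change-in-estimate rule: "relevant characteristics which change the vaccine effect by ≥1% (including risk status and sex").
- **Onset indicator** (Missing data): "An interaction term between vaccination status and indicator for swab within 0-7days of onset will fitted". Where onset is missing, the indicator is imputed from the proportion of known onsets inside the window, "taking into account positivity for flu or other viruses and patient age".
- **Risk status** (Missing data): imputed "taking into account patient age, and vaccination history and age eligibility".
- **Vaccination date, adults** (Missing data): dates are "sampled from other vaccinated patients within the same broad age cohort" and the same swab week. The drawn date decides whether the patient counts as 1-13 days after vaccination or as fully vaccinated. This step is not needed for analyses by vaccine type.
- **Scheme** (section 3.2, Study Site Settings): Scotland's indication is "acute respiratory infection (ARI) with sudden onset within the last 7 days"; England and Wales accept onset within 10 days.

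**The concern.** An imputation model should contain every variable of the analysis model that is related to the incomplete one, including the outcome and any variable with which it interacts. Otherwise the imputed records carry a zero association where the analysis looks for a real one, and the estimate is a blend of the right answer and a diluted one.

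- **Onset.** Given virus result and age, the imputed indicator is independent of vaccination. The vaccination odds ratio in imputed records is then the same inside and outside the 7-day window: the interaction is zero by construction. Scheme is also absent, so a Scottish swab with missing onset could be placed beyond 7 days at the pooled rate.
- **Risk status.** Given age and vaccination, imputed risk is independent of influenza. Adjusting for it in those records removes no confounding. The onset model does use the virus result, so the plan is not consistent on this.
- **Vaccination date.** If protection is incomplete in days 1-13, recent vaccinees are over-represented among vaccinated cases. A draw that ignores case status moves some of them into the fully vaccinated group.

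This affects the main estimates, and a larger sample does not reduce it.

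**Working it through.** The protocol gives no missing shares, expected VE, coverage, risk odds ratio or recent-vaccination share, so there is no stated figure to reproduce. All inputs below are assumptions. The method is exact expected cells with data missing completely at random, one model at a time and no other covariates. A share m of records is replaced by the imputation rule as worded, the model is refitted, and VE = 1 - OR. True VE is 50%.

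**1. Onset.** Assumed: half vaccinated; 80% swabbed within 7 days; positivity in the unvaccinated 25% within and 10% beyond; VE 50% within and 0% beyond. The protocol does not say which term is reported; since section 3.5 aims at the 0-7 day window, I take VE in that window.

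Per 1,000 patients (cases/controls):
- within 7 days: unvaccinated 100/300, vaccinated 57.14/342.86;
- beyond 7 days: 10/90 in each group.

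Imputed probability of being within the window:
- cases: 157.14/177.14 = 0.887;
- controls: 642.86/822.86 = 0.781.

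Within-window cells at m = 40%:
- vaccinated cases: 0.6 × 57.14 + 0.4 × 67.14 × 0.887 = 58.11;
- unvaccinated cases: 60 + 0.4 × 110 × 0.887 = 99.03;
- vaccinated controls: 205.71 + 0.4 × 432.86 × 0.781 = 340.98;
- unvaccinated controls: 180 + 0.4 × 390 × 0.781 = 301.88.

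OR = (58.11 × 301.88)/(99.03 × 340.98) = 0.519, so VE = 48.1%. The imputed records alone give (67.14 × 390)/(110 × 432.86) = 0.550, or 45.0% in both windows.

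Other inputs:
- m = 20%: 49.0%;
- equal VE in both windows, m = 40%: 49.8%;
- most extreme set tried (70% within, no VE beyond, m = 40%): a shift of -3.4 points.

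With vaccination status added, VE is 50.0%.

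**2. Risk status.** Assumed: 25% at risk; coverage 20% (not at risk) and 60% (at risk); positivity 20% in unvaccinated patients not at risk; current vaccination included as a predictor. Take a risk OR of 1.6. Ignoring risk, vaccinated cases/controls are 41.67/258.33 and unvaccinated 148.57/551.43 per 1,000. The crude OR is (41.67 × 551.43)/(148.57 × 258.33) = 0.599, a VE of 40.1%. That is what imputed records give after adjustment, because imputed risk is unrelated to influenza within vaccination group. Refitted on the mixture:

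| Risk OR | 20% missing | 40% missing |
|---|---|---|
| 0.6 | 51.6% | 53.2% |
| 0.8 | 50.8% | 51.5% |
| 1.0 | 50.0% | 50.0% |
| 1.25 | 49.2% | 48.3% |
| 1.6 | 48.1% | 46.2% |
| 2.0 | 47.1% | 44.1% |

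With the influenza result added, VE is 50.0% in every row. If vaccination history does not cover the current vaccine, a separate set of assumed inputs gave shifts 1.6 to 2.2 times as large.

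**3. Vaccination date.** Assumed: half vaccinated; positivity 20% in the unvaccinated; VE 0% in days 1-13; 10% of vaccinees recent; dates missing in 30% of vaccinees.

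Per 1,000 (cases/controls): unvaccinated 100/400, recent 10/40, fully vaccinated 50/400. The donor pool gives 50/500 = 10% recent to cases and controls alike.
- fully vaccinated cases: 0.7 × 50 + 0.3 × 60 × 0.9 = 51.2;
- fully vaccinated controls: 0.7 × 400 + 0.3 × 440 × 0.9 = 398.8.

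OR = (51.2 × 400)/(100 × 398.8) = 0.514, so VE = 48.6%. Matching on case status restores 35 + 0.3 × 60 × (50/60) = 50 cases and 280 + 0.3 × 440 × (400/440) = 400 controls, so VE = 50.0%.

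Other inputs: 10% recent and 10% missing, 49.5%; 30% recent and 30% missing, 45.9%.

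**The case against.** A reader might infer that VE is certain to move by more than a 1% threshold that the plan itself sets. The documents do not support that. They give none of the inputs, and many plausible sets stay under 1 point, for example a risk OR between 0.8 and 1.25 with up to 20% missing. The 1% in Flu TNCC decides which covariates stay in the model. It is not a tolerance for bias, and the plan does not say whether it is absolute or relative.

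Other points in the plan's favour:

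- The first planned sensitivity analysis drops records with unknown onset or missing items. Under data missing completely at random it would be unbiased and could expose the shift. That stands, but it does not correct the main estimate.
- The lists of predictors may not be exhaustive, and an analysis plan that is not shown may extend them. That stands as a caution. The concern is with the predictors and donor cells that the protocol itself chose to name.
- The date hot-deck has narrow scope. LAIV-eligible patients aged 2-17 without a date are excluded (section 3.6), and it is not needed for analyses by vaccine type. Undated vaccinations plausibly arise mainly in Wales, where the GP supplies status and some is self-reported. Most vaccine is delivered from late September to November (section 3.3), so a large recent share is unlikely over a full season. All of this stands; the share could be higher early in the season.

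**Conclusion.** The structural point holds for all three models; the onset model is the clearest, because it imputes one half of an interaction while ignoring the other. Direction: VE within 0-7 days is drawn towards VE beyond 7 days; fully vaccinated adult VE is drawn towards VE in days 1-13; risk status can bias VE either way, and only if it is kept in the model and related to influenza.

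The size cannot be settled from the documents. The figures above rest on a true VE of 50%, data missing completely at random and one fault at a time. They show shifts that are negligible with little missing data or weak associations, and reach several points only when a large missing share meets a strong association. This is worth correcting before analysis because imputation is intended for the main estimates and the remedy is cheap, not because a material bias has been shown.

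**What to change.** Amend the Missing data text of section 3.10:

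1. **Onset indicator:** impute from influenza result, vaccination status and their interaction, age group and scheme, keeping the other-virus result already listed.
2. **Risk status:** add influenza result, and state that vaccination history includes the current season's vaccine.
3. **Adult vaccination date:** draw donors within age cohort, swab week and case/control status. Pool adjacent weeks only where donors are too few, and repeat the draw in each imputed dataset.

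Reporting the missing share for each item beside the main VE would let readers judge how much the imputation matters.

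The cost is a few words and imputation code; no new data are needed. The downside is sparser donor cells, chiefly among vaccinated cases, and a slightly looser match on calendar time where weeks are pooled.

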**Sensitivity analyses**

1. Exclusion of individuals with unknown onset date and missing data items.
2. Restriction to patients with Asthma/COPD exacerbation in RCGP data only, and/or exploration of indicators for swabbing (ARI/ILI/COVID-like illness).
3. Inclusion of SARS-CoV-2 positive cases, with/without adjustment for Autumn 2023 COVID-19 vaccination status.

**Sample size**

All eligible patients will be included. Expected cell counts of vaccinated cases, vaccinated controls, unvaccinated cases, unvaccinated controls will be calculated. If any expected cell count is below 10, the sample size is deemed too small to produce reliable estimates and VE will not be published.

**4. Dissemination of results**

First V/E estimates (intra-seasonal) using the test-negative design will be disseminated among the research team and to WHO as part of the GIVE report early during the influenza season (early Jan of the influenza season) followed by the end of season analysis. We would envisage papers to be written at the end of the season following presentation of results at JCVI and VEBIS.

